**Expedited Review**

**Funding: Physicians' Foundation; Grants & contracts sponsor # 223216**

**I. Hypotheses and Specific Aims:**

We will conduct a randomized controlled trial to evaluate if wearing a Smartwatch improves overall well-being among physicians, and if so, in which dimension of well-being (e.g., fatigue, stress, overall quality of life, burnout). Additionally, we will explore if data from Smartwatches can predict subsequent well-being among physicians.

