**Hypothesis:**

1. Physicians with individualized access to their energy levels, oxygen level, respiratory rate, stress levels, sleep patterns, and heart rate will engage more frequently in behaviors that mitigate stress, resulting in improved well-being.
2. Fatigue, stress, and overall quality of life will improve while burnout will be less impacted by wearing a Smartwatch.
3. Physiologic parameters, collected from Smartwatches, will relate to physician's subsequent endorsement of symptoms of fatigue, stress level, and overall quality of life more closely than their measured symptoms of professional burnout.

In this study, physicians will be asked to wear a Smartwatch and answer a survey at baseline, 3-, 6-, 9-, and 12-months. We will determine if physicians who wear a Smartwatch and have access to its data experience greater improvements in their well-being relative to physicians not wearing a Smartwatch (control group). In addition, we will collect data from the Smartwatches to determine if we can utilize this data to predict subsequent level of well-being. We will build the

infrastructure and a HIPAA compliant de-identified dataset which includes (i) continuous physiology measures (from Smartwatches; raw data gathered for every 15-second epoch) and (ii) survey responses. We will use this dataset to develop predictive models for well-being derived from physiologic measures. Prediction models established using the cohort in Arm 1 will be validated in the cohort in Arm 2 after they cross-over (at the 6-month time-point) and begin using the Smartwatch.

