### **IV. Research Methods**

#### **A. Outcome Measure(s):**

Overall well-being as measured by the Well-Being Index

Overall Burnout, emotional exhaustion, and depersonalization, as measured by the Maslach Burnout Inventory

Quality of life as measured by a Linear Analogue Self-Assessment scale

Depressive symptoms as measured by the PROMIS measure 4a shortform

Stress as measured by the Perceived Stress Scale

Fatigue as measured by the Epworth Sleepiness Scale

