#### **F. Data Analysis Plan:**

For Aim 1, we will compare changes in outcome variables between Arm 1 (Smartwatch Intervention) and Arm 2 (Control group) at 6 months. Then, we will explore the durability of the benefits of having a Smartwatch for 12 months, by examining levels of well-being among Arm 1 participants at the 6- and 12-month mark. We will use generalized estimating equations to account for the repeated-measures design. Tests will be 2-sided, and we will use the intent-to-treat principle in analyses.

To determine whether continuous physiological measures (measured from Smartwatches) contain a 'signal' that predicts physician well-being, and if so in which dimensions. We will construct Probabilistic Graph Models (PGMs) for low overall well-being (score  $\geq 2$ ), burnout (score of  $\geq 27$  on emotional exhaustion scale or score of  $\geq 10$  on the depersonalization score), low quality of life ( $\geq \frac{1}{2}$  SD below the mean), high stress (score  $\geq 17$ ), and high fatigue (score  $\geq 11$ ). We will derive dynamics for these dimensions of well-being using dynamic Bayesian networks (DBN). Data from Arm 1 will be used to train MTL models to predict risk of low well-being, burnout, low QOL, high stress, and high fatigue in the next quarter. Models will be tested and retrained using data from subsequent assessments. We will then evaluate the predictions using data from Arm 2 (control). Standard metrics of model performance (e.g., AUC, sensitivity, specificity) will be reported. Predictor variables will be ranked by the relative importance in making predictions, and the top 10 predictors (a heuristic for simplicity in deriving easily interpretable predictions in English sentences) will comprise Core Well-being Factors. We aim to achieve predictive accuracies > 70%.

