| Study Title or Ad Header:
(for studies with lengthy titles, it is acceptable and appropriate to abbreviate the title)                                  | 
 
• Smartwatch Study for Physicians
 
• Smartwatch and Physician Well-Being
 
• Smartwatch and Physician Well-Being: Are Wearables Part of the Solution?
 
                                                                                                                                                                                                                                                          |
| Purpose of the Research Study:
(recommend using the word "research")                                                                                   | 
 
• The purpose of the study is to determine if wearing a Smartwatch and having access to its data improves physician well-being in any dimension. A secondary purpose is to determine whether data recorded from Smartwatches contain a 'signal' that predicts physician well-being.
 
                                                                                                                                           |
| Main Procedures Involved:                                                                                                                                        | 
 
• Physicians in this study will be asked to wear a provided Smartwatch and answer a survey at baseline, 3-, 6-, 9- and 12-months.
 
• If you are interested in a free, Garmin Smartwatch consider enrolling in the Physician Smartwatch research study. In addition to wearing the watch, participating physicians will be asked to complete surveys at baseline, 3-, 6-, 9- and 12-months
 
        |

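### The aims put overall well-being first, but eight outcomes are left unranked, the recruitment text counts any dimension, and the Aim 1 comparison contains no contrast that would answer Hypothesis 2

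*Protocol*

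**What the plan says.** - **Protocol, I. Hypotheses and Specific Aims.** The trial is to evaluate whether the watch "improves overall well-being among physicians, and if so, in which dimension of well-being". Study Aim 1 and section G (Summarize Knowledge to be Gained) repeat the same and-if-so order, without the word overall.
- **Protocol, IV.A Outcome Measure(s).** The first entry is "Overall well-being as measured by the Well-Being Index". It is followed by "Overall Burnout, emotional exhaustion, and depersonalization, as measured by the Maslach Burnout Inventory", then "Quality of life as measured by a Linear Analogue Self-Assessment scale", "Depressive symptoms as measured by the PROMIS measure 4a shortform", stress on the Perceived Stress Scale and fatigue on the Epworth Sleepiness Scale. That makes eight outcomes, none labelled primary or secondary.
- **Protocol, IV.F Data Analysis Plan.** For Aim 1, changes in the outcome variables are compared between arms at 6 months, with generalized estimating equations for the repeated measures. "Tests will be 2-sided, and we will use the intent-to-treat principle in analyses". No order of testing, alpha level or success criterion is given.
- **Protocol, H. Advertising Components Submission Form.** The purpose is given there as whether wearing the watch and "having access to its data improves physician well-being in any dimension".
- **Protocol, Hypothesis 2.** Fatigue, stress and quality of life are expected to improve "while burnout will be less impacted by wearing a Smartwatch".

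**The concern.** Two separate matters are left open.

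The first is which question the trial answers. Suppose the Well-Being Index shows no difference at 6 months and the stress score is significant. Under the opening section the leading question has failed and the dimension question does not arise. Under the recruitment text the watch has worked. The outcome list and the analysis plan do not say which reading governs, so the main claim could be settled after seeing which outcome crossed the threshold.

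The second is Hypothesis 2. It states that the effect on burnout is smaller than the effects on three other dimensions, which is a statement about a difference between effects. Comparing the arms on each outcome gives one effect per outcome but no test or interval for the difference between them. A significant stress result beside a non-significant burnout result does not show that the two effects differ, and that pattern could be taken as support for the hypothesis when the effects are equal.

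**Working it through.** **Inputs from the protocol.** Eight outcomes (IV.A); two-sided tests (IV.F); up to 184 enrolled and 15% dropout (IV.B). This gives 184 × 0.85 / 2 = 78.2, about 78 evaluable per arm.

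**Assumptions, not in the protocol.** Alpha 0.05 per outcome; 1:1 allocation; outcomes treated as standardised scores with approximately normal test statistics; a common inter-outcome correlation ρ, shown over a range; true effects of 0.2-0.45 SD where an effect is assumed. The figure of 184 cannot be reproduced, because no effect size, SD, power or powered outcome is given with it.

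**1. No true effect on any outcome.** Under independence the chance of at least one significant result of eight is 1 − 0.95^8 = 33.7%, and in the beneficial direction only 1 − 0.975^8 = 18.3%. Independence is not realistic here: IV.F defines burnout from the emotional exhaustion and depersonalization scores, so three of the eight outcomes overlap. Simulating eight equally correlated z-statistics (400,000 draws) gives:

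| ρ | At least one significant, either direction | At least one significant benefit |
|---|---|---|
| 0.3 | 30% | 15% |
| 0.5 | 25% | 13% |
| 0.7 | 19% | 9% |
| 0.8 | 16% | 8% |
| One test only | 5% | 2.5% |

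The right-hand column is the relevant one for a claim of improvement.

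**2. Equal true effects, Hypothesis 2 false.** Give fatigue, stress, quality of life and one burnout score the same standardised effect d. Each z-statistic has mean d × √(78/2). Count the trials in which at least one of the three is significant for benefit and burnout is not:

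| d | ρ = 0.3 | ρ = 0.5 | ρ = 0.7 |
|---|---|---|---|
| 0.2 | 33% | 27% | 20% |
| 0.3 | 37% | 30% | 23% |
| 0.45 | 18% | 17% | 14% |

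The range is 14-37%. For one named dimension against burnout, rather than any of three, it is 9-20%.

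**3. What a direct contrast could show.** The difference between two standardised outcomes has SD √(2(1−ρ)). With 78 per arm and a true gap of 0.3 SD, power ≈ Φ(0.3 × √39 / SD − 1.96), where 0.3 × √39 = 1.873:

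- ρ = 0.3: SD 1.183, power 35%.
- ρ = 0.5: SD 1.000, power 47%.
- ρ = 0.7: SD 0.775, power 68%.

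These figures are for one dimension against burnout. If the three dimensions are averaged first, the SD is √((1−ρ)(1 + 1/3)), that is 0.966, 0.816 and 0.632, and power for the same gap is 49%, 63% and 84%.

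**The case against.** The strongest reply is that the order of testing, multiplicity control and a model for Hypothesis 2 are ordinary SAP content, and the SAP is not at hand. That stands as far as it goes: the absence of an adjustment method is not the point. What remains is in the protocol itself. Its statements of purpose differ, its outcome list has no primary, and its comparative hypothesis is not matched by the comparison it describes. Choosing the primary outcome is a protocol decision.

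A reader might infer more than the text supports in four ways.

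- *That a benefit in any dimension is the trial's success rule.* Those words occur only in the recruitment form. The opening section, Aim 1 and section G all use the and-if-so order, so this is a conflict to be resolved, not a declared rule.
- *That the eight outcomes are declared co-equal.* They are unranked. The Well-Being Index stands first in the list and matches the leading objective, which suggests an intended order that was never written down.
- *That a useless watch would produce a false claim in a third of trials.* The 33.7% needs independent outcomes and counts harm as well as benefit.
- *That Hypothesis 2 will be judged by significant versus not significant.* The protocol does not say so. It only describes nothing else that would answer it.

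It is also fair to object that making the Well-Being Index primary moves the very dimensions Hypothesis 2 expects to change into second place. That is a real cost and is carried into the fix.

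**Conclusion.** The concern holds in limited form. The protocol does not fix one primary question for Aim 1, and its described Aim 1 comparison does not address Hypothesis 2.

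At an assumed two-sided 0.05 per outcome and correlation 0.3-0.8, the chance of at least one falsely significant benefit is about 8-15%, roughly three to six times the 2.5% of a single test (16-30% against 5% if either direction counts). Under equal true effects, a pattern resembling Hypothesis 2 would appear in about 14-37% of trials. That range assumes effects of 0.2-0.45 SD, 78 evaluable per arm, 1:1 allocation and correlation 0.3-0.7. Both figures show the size of the problem under these assumptions. Neither predicts how the trial will be reported. The change should be made, and it needs no new data.

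**What to change.** 1. In IV.A, name the Well-Being Index at 6 months as the single primary outcome, in line with the opening section. Label the other seven secondary, and report them either as estimates with confidence intervals or under a stated multiplicity rule. Holm after a significant primary result is one reasonable choice among several.
2. In section H, reword the statement of purpose to match.
3. In IV.F, evaluate Hypothesis 2 by a direct contrast. Standardise the outcomes, align their signs so that positive means benefit, and estimate the difference between the effect on fatigue, stress and quality of life and the effect on one named continuous burnout score, for example emotional exhaustion. State whether the three dimensions are averaged or contrasted one by one. Report the difference with a confidence interval. A continuous score is needed because the only burnout definition in IV.F is a binary cut-off written for Aim 2.

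**Cost.** Protocol wording and one joint model; no extra participants, visits or survey items. Dimension-specific claims become secondary. The contrast has limited power, about 35-68% for a true gap of 0.3 SD between one dimension and burnout and somewhat more if the three are averaged, so it should be read as an estimate and a non-significant contrast should not be read as equal effects.

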**Study Aims:**

1. To determine if wearing a Smartwatch and having access to its physiological data (e.g., sleep, step count, activity, breathing reminders) improves well-being, and if so which well-being dimensions.
2. To determine whether continuous physiological measures (measured from Smartwatches) contain a 'signal' that predicts physician well-being, and if so in which dimensions.

**Hypothesis:**

1. Physicians with individualized access to their energy levels, oxygen level, respiratory rate, stress levels, sleep patterns, and heart rate will engage more frequently in behaviors that mitigate stress, resulting in improved well-being.
2. Fatigue, stress, and overall quality of life will improve while burnout will be less impacted by wearing a Smartwatch.
3. Physiologic parameters, collected from Smartwatches, will relate to physician's subsequent endorsement of symptoms of fatigue, stress level, and overall quality of life more closely than their measured symptoms of professional burnout.

In this study, physicians will be asked to wear a Smartwatch and answer a survey at baseline, 3-, 6-, 9-, and 12-months. We will determine if physicians who wear a Smartwatch and have access to its data experience greater improvements in their well-being relative to physicians not wearing a Smartwatch (control group). In addition, we will collect data from the Smartwatches to determine if we can utilize this data to predict subsequent level of well-being. We will build the

infrastructure and a HIPAA compliant de-identified dataset which includes (i) continuous physiology measures (from Smartwatches; raw data gathered for every 15-second epoch) and (ii) survey responses. We will use this dataset to develop predictive models for well-being derived from physiologic measures. Prediction models established using the cohort in Arm 1 will be validated in the cohort in Arm 2 after they cross-over (at the 6-month time-point) and begin using the Smartwatch.

## **II. Background and Significance:**

Upwards of 40% of physicians have burnout. Physicians at the front lines of caring for patients with COVID-19 are at highest risk, and at least since 2011 burnout has been more prevalent among physicians than other US workers. Multiple systematic reviews and meta-analyses have concluded clinician burnout impacts quality of care in important ways. For example, studies of clinicians have found burnout is independently associated with medical error, medical malpractice suits, poor professionalism, absenteeism, low job performance, less favorable cost conscious attitudes, racial biases, lower competency, job dissatisfaction, patient dissatisfaction ratings across a variety of domains, and longer patient recovery times. Physicians with burnout are approximately twice as likely to quit their jobs and reduce clinical hours, resulting in a loss of productivity and access to care. At an organizational level burnout-attributable costs related to job turnover and reduced clinical hours among physicians alone are approximately \$7600 per physician each year with approximately \$4.6 billion in cost on a national scale. Additionally, studies have also found burnout to be independently associated with sleep impairments, alcohol abuse/dependence, suicidal ideation, and motor vehicle incidents. Physicians are at increased risk of suicide compared to the U.S. general population.

Unfortunately, burnout is underrecognized by those who suffer from it, and it typically goes undetected until physicians' performance or health deteriorates. There is a moral and business case to develop pragmatic ways to identify physicians at risk for burnout. In recognition of the broad impact of physician well-being on individuals, healthcare organizations, and society, The National Academy of Medicine's consensus study on clinician burnout (co-authored by PI [name]) "call(ed) upon leaders in health care organizations and health professions, educational institutions, as well as within the government and industry to prioritize, prevent and mitigate burnout and foster professional well-being for the overall health of individuals and the nation."

Despite these recommendations from the National Academy of Medicine, few intervention studies have been conducted to-date involving residents and physicians to guide personal and organizational strategies. In previous randomized controlled studies, funded by the Physicians Foundation, we demonstrated that professional coaching reduced overall burnout and improved quality of life and resilience among physicians. It remains unknown, however, if physicians at risk for burnout or poor well-being in other dimensions will recognize it and proactively take steps to engage in professional coaching.

In this proposed study, we plan to conduct a 2-arm randomized controlled trial evaluating the effectiveness of 6 months of wearing a Smartwatch and having access to one's physiologic data to improve well-being among physicians. There is increased ubiquity of wearable technologies such as Smartwatches, that provide quantitative measures of one's physiological functioning (e.g., heartrate, sleep cycles, sleep quality) that may serve as a real-time surveillance mechanism to

forecast impending burnout or changes in other dimensions in well-being, potentially triggering individual intervention before suffering or negative impact to patient care occurs. We anticipate that providing physicians with individualized access to their energy levels, oxygen level, respiratory rate, stress levels, sleep patterns, and heart rate will promote behaviors that mitigate stress, resulting in improved well-being.

Additionally, to preempt burnout among physicians, there is an urgent and unmet need for predicting imminent burnout. The National Academy of Medicine's consensus study on clinician burnout recommended that organizations regularly deploy surveys to measure and monitor physician well-being. Although surveys are an important tool, at best they prompt action in work units where quality of care has already suffered, and turnover or loss of productivity has already occurred due to high levels of burnout. Additionally, individuals are typically not made aware of their own level of distress because of completing an organizational survey. Physiologic parameters, collected from Smartwatches, may be able to predict burnout ahead of its observable manifestations. Such information could help individuals as well as organizations engage in proactive interventions to mitigate risk of future burnout, protecting patients and physicians. Burnout can be addressed and therefore, early identification could have a profound broad impact on physicians, patients, employers, and the global economy (improved productivity, work performance and reduced absenteeism).

### **III. Preliminary Studies/Progress Report:**

Few intervention studies have been conducted to-date involving residents and physicians to guide personal and organizational strategies. In previous randomized controlled studies, funded by the Physicians Foundation, we demonstrated that professional coaching reduced overall burnout and improved quality of life and resilience among physicians. It remains unknown, however, if physicians at risk for burnout or poor well-being in other dimensions will recognize it and proactively take steps to engage in professional coaching.

### **IV. Research Methods**

#### **A. Outcome Measure(s):**

Overall well-being as measured by the Well-Being Index

Overall Burnout, emotional exhaustion, and depersonalization, as measured by the Maslach Burnout Inventory

Quality of life as measured by a Linear Analogue Self-Assessment scale

Depressive symptoms as measured by the PROMIS measure 4a shortform

Stress as measured by the Perceived Stress Scale

Fatigue as measured by the Epworth Sleepiness Scale

#### **B. Description of Population to be Enrolled:**

Age range: 19 to 80

Up to 184 subjects enrolled at all sites

Enrollment will not be limited based on sex, gender, race or ethnicity.

Inclusion criteria: Physician (residents/fellows or practicing faculty physician) employed by the University of Colorado School of Medicine or Mayo Clinic with no anticipated departure within 18 months of enrollment. Physicians must be employed full-time or part-time (at 60% FTE or higher) and have an Android or iOS smart phone.

Exclusion criteria: Not in the age range. Not a physician employed by the University of Colorado School of Medicine or Mayo Clinic. Does not own an Android or iOS smart phone. Non-reading subjects. Residents/fellows in their last final year of their respective training program.

Residents/fellows may participate in the study, and can be vulnerable to coercion. They do, however, experience burnout and may benefit from insight into their well-being and future technology able to predict burnout so that it can be mitigated before it occurs. To protect their welfare, we will inform all participants that their decision to participate in this study is entirely voluntary and will not affect their current or future medical care, education, or training at the organization. Additionally, on the survey they may skip any question they do not feel comfortable answering. Residents / fellows may receive an e-mail invitation to participate or learn about the study from other sources. Participation will be optional.

Our power calculations account for a 15% drop-out rate due to watches getting stolen/damaged. Given the study incentives and enthusiasm of our residents and faculty physicians to address burnout and wear novel technologies, we anticipate dropouts will be minimal. In our previous intervention studies, we have been able to meet recruitment goals with survey completion rates of over 90%.

